## Abstract

**Background:**

Beginning in 2017 we have conducted a 3-arm randomised controlled trial (RCT) to determine the effectiveness of an early obesity intervention in the first two years of life using either telephone or Short Message Service (SMS) support for mothers. The trial recruited 1155 mothers from their third trimester of pregnancy. This protocol is for a new trial to build on the existing trial using the mother-child dyads retained at 24 months for recruitment to the new RCT. The aim of this new trial is to test whether use of a combination of telephone and SMS interventions is effective in promoting healthy eating and physical activity, as well as reducing child body mass index (BMI) at 3 years of age.

**Methods:**

We will conduct a parallel RCT with an estimated sample of 750 mother-child dyads retained from the existing trial at 24 months. Mothers who completed the 24 months survey, including a telephone survey and measurement of child’s height and weight will be invited to participate in the new trial. Informed consent will be obtained at the 24 months survey. The participating mother-child dyads will then be randomly allocated to the intervention (combined telephone and text messaging intervention) or the control group. The intervention will comprise three staged telephone consultations and text messages after each of the three intervention booklets is mailed to mothers at specific time-points between two and three years of child age. The main trial outcome measures include a) BMI and BMI z-score measured at 36 months, b) diet, physical activity and screen time c) cost-effectiveness, and d) feasibility and acceptability of the intervention.

**Discussion:**

This unique opportunity to link two studies will expedite project start up time, utilise existing research infrastructure and systems to run the study, and optimise the use of an already engaged population of study participants. It can address a significant knowledge gap regarding early obesity prevention for children aged 2 to 3 years. The feasibility and effectiveness of the combined telephone and SMS intervention will indicate whether this is a scaleable, broad-reach and low-cost early obesity intervention.

**Trial registration:**

The trial was registered with the Australian Clinical Trial Registry (ACTRN12618001571268) on 20/09/2018.

**Electronic supplementary material:**

The online version of this article (10.1186/s12889-019-7058-9) contains supplementary material, which is available to authorized users.

## Background

Ending Childhood Obesity is now a global health policy issue for the World Health Organisation [1]. Worldwide, the prevalence of childhood obesity increased around eight-fold in both girls (0.7 to 5.6%) and boys (0.9 to 7.8%) between 1975 and 2016 [2], with 41 million children under the age of 5 affected by overweight or obesity in 2016 [1]. About one in five Australian children aged 2–3 years [3] and one third of children aged 2–5 years [4] are affected by overweight or obesity. Promoting healthy feeding and physical activity, together with reducing screen time, are fundamental to preventing obesity among children in the first few years of life and consistent with WHO guidelines on childhood obesity prevention [1].

Although it is increasingly argued that childhood obesity prevention should begin in the early years, current evidence of effective, cost-effective and sustainable interventions is scarce. Not surprisingly, no quality evidence is found specifically targeting 2–3 year old children. Of the few intervention studies we found for children less than 5 years, most targeted children either from birth to 2 years (with an increasing focus on the first 1000 days of life) [5–7] or from 3 to 5 years of age using childcare-based interventions [8]. The most frequent intervention duration was 6 months, with outcomes focussed on dietary and physical activity behaviours rather than weight status. Very few studies used short message service (SMS) or telephone support as the main form of early intervention [1, 7]. In Australia most state health departments focus their early obesity prevention program through formal childcare services. For example, the ‘Munch & Move’ program in the state of New South Wales (NSW) aims to promote and encourage healthy eating and physical activity habits and reduce small screen recreation in young children from birth to 5 years who attend early childhood education and care services [9]. However, the Australian Bureau of Statistics showed that about 48% of 2-year-old children and 44% of 3-year-old children did not attend formal childcare services in 2014 [10]. Therefore, interventions that focus solely on childcare services may miss a large proportion of children in the target age group.

The Healthy Beginnings© program is an early obesity prevention program delivered by Child and Family Health Nurses originally through home visits in the first two years of life [11–15]. Healthy Beginnings© was found to be effective in reducing child body mass index (BMI) at 2 years of age [13], but may not be sustained in the longer term [15] nor cost-effective [16]. There is emerging evidence that interventions delivered through telephone-based counselling [17, 18] or SMS improve health behaviour [19, 20]. Since 2017, we have conducted a 3-arm randomised controlled trial (RCT) to evaluate the efficacy of using SMS or telephone support, plus mailed educational materials for mothers with newborns, as an alternative delivery model for the Healthy Beginnings© early intervention program (http://www.healthybeginnings.net.au/). The study protocol titled “A 3-arm randomised controlled trial of Communicating Healthy Beginnings Advice by Telephone (CHAT) to mothers with infants to prevent childhood obesity” was published in early 2017 [21]. Known as the CHAT trial, the interventions are being delivered from the third trimester to 2 years of age. The interventions include nine staged mail-outs over 24 months addressing key developmental milestones, followed by either nine staged telephone-support sessions by a Child and Family Health Nurse (six between the 3rd trimester to 12 months and three from 12 to 24 months), or nine sets of SMS messages. Each SMS set comprises eight messages which are sent out twice a week over a 4-week period. However, as stated in the published study protocol on the study design, further funding would be required to assess the outcomes at 24 months.

Based on the preliminary findings from the CHAT trial several advantages of using telephone support as a stand-alone program have been identified. Telephone support was seen by the mothers as more personal and increased the mother’s self-reported likelihood of identifying and addressing challenges with practising the desired health behaviours that influence healthy weight gain (detailed findings to be reported elsewhere). However, these advantages can be reduced by the time and effort spent contacting the participants. On average, the intervention nurse has needed to make 6–10 call attempts to each participant for one successful telephone support session, which is not an efficient use of resources (nurse time). On the other hand, using SMS has advantages as an efficient, simple and lower-cost method to deliver information to mothers and to respond quickly to their queries. Participants can also review responses at a time of their convenience. This is particularly useful for mothers with strong demands on their time. Despite the fact that the text messages were bi-directional, there was limited capacity for the intervention nurses to gather a detailed understanding of the challenges being experienced by mothers through SMS, and responses to mothers were likely to be brief. Thus, the combined intervention (Tel + SMS) being investigated in this new study seeks to mirror a real-life situation where interventions such as telephone support rarely occur in isolation and are often accompanied by SMS reminders and missed call messages. By combining telephone and SMS into an intervention delivery, we will be able to compensate for inherent limitations of each element and greatly improve their collective effectiveness.

Therefore, in this study protocol we are undertaking a new RCT which will be linked with the existing 3-arm RCT using the same study participants (see Fig. 1). This approach will enable us to use the 24-month survey for dual purposes in the existing 3-arm CHAT RCT (Study 1) and the new RCT (Study 2). For Study 1, the 24-month survey will measure the intervention outcome and effectiveness of either the telephone support intervention or the SMS intervention. For Study 2, the 24-month survey will be an integral part of the recruitment process and baseline data collection for this new RCT in determining the effectiveness of a combined telephone and SMS intervention.

**Fig. 1 Fig1:**
[figure not shown]
Study Designs of Study 1 and 2

### Aims and hypotheses

The aim of the study is to evaluate the effectiveness and cost-effectiveness of combined telephone and SMS intervention targeting mothers of children between 2 and 3 years of age in promoting healthy eating and physical activity, as well as reducing child BMI at 3 years of age.

We hypothesise that, in comparison with usual care, the Tel + SMS intervention will improve the following main outcomes:lower child BMI at age 3 years;lower child screen time (i.e. TV viewing time) and increased physical activity;better dietary quality (i.e. greater intake of fruits/vegetables) at 3 years;improved mothers’ healthy eating and physical activity; anddemonstrated cost-effectiveness of the intervention.

The study aims to specifically address the following research questions:
*Will a combined telephone and SMS support early intervention with mailed health resources delivered to mothers with children between 2 to 3 years significantly reduce children’s BMI at age 3 years?*

*Will a combined telephone and SMS support early intervention with mailed health resources delivered to mothers with children between 2 to 3 years significantly improve child eating behaviours, and significantly decrease the prevalence of obesity-related risk behaviours at 3 years of age?*

*What are the incremental costs and benefits of the combined telephone and SMS support early intervention from a health funder perspective?*

*Is the intervention feasible and acceptable and to what extent is the intervention likely to be translated into practice?*

## Methods

### Design

A parallel RCT using the study participants from the existing CHAT trial (Fig. 1).

### Setting

The study will be carried out in four local health districts in New South Wales, Australia, including the Sydney, South Eastern Sydney, South Western Sydney and Southern NSW Local Health Districts.

### Participants and recruitment

As shown in Fig. 2, 5 weeks before the participating child turns 2 years old in the existing CHAT trial, their mother or primary caregiver will be sent a letter of invitation with information about the 24-month survey and Study 2. A week later, a text message will be sent out to remind participants of the 24-month survey. Three weeks before the child reaches 2 years, a market survey interviewer will contact participants on behalf of the project team to conduct the 24-month telephone survey. A telephone script will be used to ensure consistency and documentation across all interviewers. Participants will be asked to verbally consent to participation prior to commencing the survey. Once verbal consent is obtained, the interviewer will conduct the 24-month survey (i.e. baseline for Study 2) using the computer-assisted telephone interview (CATI).

**Fig. 2 Fig2:**
[figure not shown]
Recruitment flow chart

During the last section of the telephone survey, interviewers will invite participants to receive a home visit by a research assistant (RA) for face-to-face measurement of their own and their child’s height and weight. Verbal consent will be initially requested by the interviewer, however, once the RA has organised the home visit, they will ask for the participant’s written consent before conducting the measurements. Overall, participants will be offered the following options for participation:Only consent to complete the 24-month telephone surveyConsent to participate in the 24-month telephone survey and the home visit for the anthropometric measurementsConsent to participate in options 1 and 2, and also the new RCT to receive the intervention at 2 to 3 years of age; orNo consent to participate in any component.

When the RA and the participating mother meet face-to-face to measure her and her child’s height and weight, the RA will first revisit the Participant Information Sheet and Consent Form and answer any questions that the participant may have. The RA will then obtain the participant’s written consent for the new trial to support the verbal consent already obtained.

### Inclusion criteria

Inclusion for Study 2 is limited to participants of the existing CHAT trial, in which the participating women at the time of original recruitment were aged 18 years and over, were at 28–34 weeks of pregnancy, were able to communicate in English, had a mobile phone, lived in the recruitment areas, were able to give informed consent and did not have any severe medical conditions based on advice given by their doctors.

### Exclusion criteria

Mothers and children will be excluded from the study if they have moved out of the study area, or they have developed a severe medical condition since commencing the study.

### Sample size

For the existing Study 1 the sample size required was previously presented in the published research protocol (1056 mothers: 352 in each of the 3 arms of the study) [21]. A total of 1155 mothers were recruited into the trial exceeding the required sample size by 100 mothers. We originally estimated that a total sample size of 792 (264 per arm × 3) was needed at 2 years to have sufficient power to detect a difference in child BMI of 0.38 kg/m^2^.

For Study 2, we will need a total sample size of 506 (253 per arm × 2) by the end of the study (at 3 years of age). This would allow us to detect a difference of 0.40 kg/m^2^ in mean BMI (SD = 1.60 based on Healthy Beginnings Trial) at the 2-sided 5% significance level with 80% power. This effect size is achievable based on the findings from a 6-month intervention study in the US that detected a decrease in BMI of 0.40 kg/m^2^ with children aged 2–5 years [22]. Allowing for a conservative 15% loss to follow-up between 2 and 3 years, we will need around 600 participants at 2 years of age. This sample size will also give enough power to detect differences in other main outcomes (e.g., a difference of 0.3 in the mean number of daily serves of fruit or vegetables).

### Randomisation

After completing the 24-month (baseline) survey and measurement, participating mothers will be randomly allocated to either the intervention (Tel + SMS) or the control group (Control 2). Randomisation will take place using a web-based tool (http://www.randomization.com/). The intervention allocation scheme will be generated using random permuted blocks stratified by the group allocation in Study 1 (see Fig. 1). The use of stratified randomisation is to ensure that any carry-over effect of the CHAT intervention of Study 1 will be equally distributed between treatment groups in Study 2.

### Intervention (Tel + SMS) protocol

The intervention will be guided by the Health Belief Model [23], and uses motivational interviewing techniques to facilitate behaviour change [18]. The intervention aims to improve mothers’ parenting behaviours and set up healthy behaviours (i.e., healthy feeding practices, active play and reduced screen time). Telephone support will consist of protocol-based sessions. A telephone protocol and manual will be developed to ensure consistency of intervention delivery based on our current trial. The main content is in keeping with the Australian Dietary Guidelines, early childhood developmental guidelines and the Australian 24-Hour Movement Guidelines for the Early Years (Birth to 5 years) [24]. Telephone sessions will be delivered by a clinician (Child and Family Health Nurse/midwife) trained in telephone support, health behaviour change strategies, and child development. Based on our current trial experience, we anticipate that each telephone session will be ~ 20 min in duration.

The Tel + SMS intervention will be delivered between age 2 and 3 years (see Table 1). Once random allocation is completed, the intervention group will receive scheduled support across 3 time-points (24–28, 28–32, and 32–36 months). At each time-point, participants will be sent one of the three intervention booklets that provide information on key developmental milestones associated with promoting behaviours for healthy weight gain. The intervention booklets will be developed according to the key messages (see Table 1) that support child development during this age of a child’s life. Following a mailed intervention booklet, participants will receive a telephone support call from a research clinician. The clinicians will employ a motivational interviewing approach and aim to set goals, build skills and knowledge, address barriers, and manage any anxiety or stress which may act as a barrier to health behaviour change.

**Table 1 Tab1:** Main focus and contents of the staged early intervention and sample of the text messages

Component/focus	Main contents	Sample of SMS
Repeated exposure to healthy foods, limiting exposure to non-core foods	Recommended dietary intake of food groups, food label reading, healthy food environments, eating family meals, oral health, managing external influences on dietary intake	“Messy eating and playing with food are normal parts of [baby’s name] development when learning to eat independently. Check out the Healthy Beginnings booklet for tips to help with feeding”
Promotion of choosing water as a drink and exclude sugar sweetened beverages	Encourage drinking healthy drinks from a cup, oral health	“Drinking water from a cup is the only drink that [baby’s name] needs. Fruit juice, soft drinks, flavoured milk can cause teeth decay”
Promotion of responsive complementary feeding strategies	Hunger and satiety cues, strategies to manage fussy eating behaviours	“At 2–3 years it is normal for toddlers’ appetites to go up and down. Keep on providing a variety of healthy foods and it is up to [baby’s name] to decide how much food to eat.”
Promotion of incorporating physical activity into children’s daily routine	Encourage active play, support the development of Fundamental Movement Skills, developmental milestones, child safety	“It is recommended that toddlers should be active every day for at least 3 h throughout the day. Playing in the park, kicking a ball or catching & throwing are some fun activities”
Promotion of reduction in any screen-time (TV, DVDs, computers, smartphones, iPads/tablets)	Avoid any screen time, encourage quiet (reading, singing, music, drawing, dress-ups) and active (dancing, playground, running, walking)	“Your baby needs to be active every day and does not need any screen time. Playing with other children in a safe, supervised area will help them develop socially.”
Promotion of fostering healthy sleeping habits	Developing a sleep schedule, developing a bedtime routine, understanding sleep patterns	“At 2–3 years toddlers need to sleep between 12 and 13 h a day. The Healthy Beginnings booklets have tips on how to develop a healthy sleep routine. For more support send us a text”

Key Features of the intervention delivery mode:

• The intervention will be delivered at 24–26, 28–30, and 32–34 months

• A Healthy Beginnings booklet will be sent to participants which provides information on relevant topics for each milestone

• Two SMSs will be sent per week for 8 weeks tailored to the child’s development and main focus

• Three telephone calls using Anticipatory Guidance to deliver the content at each intervention stage by trained Child and Family Health Nurses

In addition, participants will also receive two text messages per week for the next 8 weeks (i.e., 16 SMS messages to enhance and reinforce the support provided in the intervention booklet and telephone session). The text messages will be generated and sent using a dedicated, secured web-based software that was used in the existing trial (Study 1). This software has the ability to automate, schedule and personalise the text messages delivered (based on the child’s age) to deliver age appropriate information and to address the message using the child’s and mother’s name. Information can be further tailored at any point during the intervention. Further, a key feature of the SMS program is that the messages are bi-directional so mothers are able to respond to text messages sent and receive a response from the clinicians delivering the program. In addition to sending SMSs on key developmental milestones, mothers will also be reminded of booking telephone calls with our research clinicians. Incoming SMSs will be reviewed daily (except for weekends and public holidays) by the research clinicians.

### Control arm

In the control group mothers will receive usual care, which all mothers (including the intervention mothers) receive if needed from the service. Further, this group will also receive two booklets that do not contain any information relating to the intervention resources. The booklets will provide information on other aspects of child development such as toilet training, language development and sibling relationships. This strategy is used to maximise mothers’ engagement in the study and to reduce attrition rates.

### Retention strategies

We have developed a set of effective cohort retention strategies through the existing CHAT trial [21]. For example, we will send a thank-you card and birthday card for all participating family and children. After hours telephone support calls will be available for mothers who have been back to work in the intervention group.

### Data collection

The 24-month survey will be collected by computer-assisted telephone interviewing (CATI) and home visiting for anthropometric measurements by an RA who is blinded to treatment allocation.

### Primary outcomes

The primary outcome is child’s BMI (weight/length^2^; kg/m^2^) or BMI z-score at 3 years of age as used in the previous Healthy Beginnings Trial [13, 15]. Child’s height and weight (and hence BMI, or BMI z-score) will be measured according to the measurement protocol (Additional file 1) in the home by RAs blinded to treatment allocation. Two measures of height will be taken to the nearest 0.1 cm using a portable stadiometer. Measurements of weight (to the nearest 0.1 kg) will be taken using digital scales with the child wearing light clothing and no shoes.

### Secondary outcomes

At 3 years, secondary outcomes will include child’s and mother’s screen-based activities (e.g., watching TV), fruit and vegetable consumption and other eating habits.

Child’s eating habits and screen-based activities: These measures will be reported by their mother using a validated short food frequency questionnaire (FFQ) and validated activity questions [25, 26].

Mother’s nutrition and physical activity: These outcomes will be assessed based on the questions from the NSW Health Survey Program questionnaire which was used previously in the Healthy Beginnings Trial [13, 15].

### Socio-demographic characteristics at baseline (24 months)

We will collect or update socio-demographic data if there is any change to demographic characteristics (e.g, employment status, marital status).

### Data analysis

CONSORT guidelines for reporting randomised controlled trials will be followed to analyse and report the results. Intention-to-treat principles will be adopted to analyse all outcomes. The primary analysis for Study 2 will be adjusted for the stratification by Study 1 treatment group, as per CONSORT guidelines. For continuous variables, such as BMI, or BMI z-score, means will be compared using linear regression. For binary categorical variables, logistic regression model will be used. Secondary analyses will additionally adjust for exact age, and also will use mixed model and multiple imputation to assess the effect of loss to follow-up as used in the previous Healthy Beginnings Trial [13]. Mean differences of BMI or BMI z-score between the intervention and control groups and adjusted odds ratio (AOR) with 95% confidence interval (CI) will be reported.

### Issue of ‘contamination’ and ‘carry-over effect’ from study 1 to study 2

To assess the level of contamination in the control group and also to test whether the intervention group is receiving additional information, we will ask mothers in both groups to report their sources of information on healthy child feeding and active play. Study 1 intervention will be included in the multivariable regression models to adjust for its effect. In our previous study we demonstrated that, without further intervention, the early intervention effects diminish over time [15], so any carry-over effect from Study 1 to Study 2 should be small. Even if there is a carry-over effect, it will be balanced between the intervention and control groups by the stratified randomisation.

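### The primary model for 36-month BMI names only Study 1 group as a covariate and leaves out the 24-month BMI measured before randomisation, forgoing precision at no saving

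*Protocol article*

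**What the plan says.** The Data analysis section of the protocol article gives the primary model in two sentences: "The primary analysis for Study 2 will be adjusted for the stratification by Study 1 treatment group, as per CONSORT guidelines" and "For continuous variables, such as BMI, or BMI z-score, means will be compared using linear regression". It then sets out what comes on top: "Secondary analyses will additionally adjust for exact age, and also will use mixed model and multiple imputation to assess the effect of loss to follow-up". The paragraph on contamination and carry-over mentions multivariable regression models, but the only term it names for them is the Study 1 intervention. Neither 24-month BMI nor 24-month BMI z-score is named as a covariate anywhere in the article.

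The value is nonetheless collected before allocation. In the abstract: "Mothers who completed the 24 months survey, including a telephone survey and measurement of child’s height and weight will be invited to participate". Under Randomisation: "After completing the 24-month (baseline) survey and measurement, participating mothers will be randomly allocated to either the intervention (Tel + SMS) or the control group". The Background describes the role of that contact: "the 24-month survey will be an integral part of the recruitment process and baseline data collection for this new RCT". Randomisation is stratified by Study 1 group and by nothing else.

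**The concern.** A child's BMI at 24 months can be expected to predict the same child's BMI at 36 months. Under the planned sequence, each randomised child should have that value recorded before allocation. The primary model as written does not use it.

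Two things are at stake. First, variation between children that the 24-month value could explain stays in the residual, so the primary confidence interval is wider than it need be. Second, because randomisation is not stratified on BMI, the arms are balanced on 24-month BMI only by chance, and the primary estimate carries part of any imbalance. The Study 1 term does not solve this. It removes mean differences between the Study 1 groups, not differences between children within a group.

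**Working it through.** **Inputs from the Sample size section.** Target difference 0.40 kg/m²; SD 1.60; two-sided 5% level; 80% power; 253 per arm (506 in total) at 3 years; 15% loss; around 600 at 2 years.

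**Input that has to be assumed.** r, the within-arm correlation between 24-month and 36-month BMI. The article does not give it, so a range is shown.

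**Step 1: reproduce the plan's own figure.** n per arm = 2 × (1.960 + 0.842)² × 1.60² / 0.40² = 251.2, so 252 per arm. The t-test version gives 252.13, which rounds up to the stated 253. With 253 per arm, SE = 1.60 × √(2/253) = 0.142 and power = Φ(0.40/0.142 − 1.960) = 80.3%. Allowing for loss, 506/0.85 = 595.3, so 596, against the stated figure of around 600. The sample size is right for an analysis that uses the full SD, that is, without baseline BMI.

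**Step 2: add the 24-month value.** The residual SD becomes 1.60 × √(1 − r²), and SE = 1.60 × √(1 − r²) × √(2/253). The variance of the treatment effect falls by r².

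| Assumed r | Variance reduction | Residual SD | SE | 95% CI half-width | Power for 0.40 | Difference detectable at 80% power |
|---|---|---|---|---|---|---|
| 0 | 0% | 1.600 | 0.142 | 0.279 | 80.3% | 0.399 |
| 0.3 | 9% | 1.526 | 0.136 | 0.266 | 83.8% | 0.380 |
| 0.5 | 25% | 1.386 | 0.123 | 0.241 | 90.1% | 0.345 |
| 0.7 | 49% | 1.143 | 0.102 | 0.199 | 97.6% | 0.285 |
| 0.8 | 64% | 0.960 | 0.085 | 0.167 | 99.7% | 0.239 |

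**Step 3: effect of a chance imbalance.** Assume the baseline SD is also 1.60. One standard error of the between-arm difference in 24-month BMI is then 1.60 × √(2/253) = 0.142 kg/m². With equal SDs at the two ages, the estimate without baseline adjustment shifts by r × 0.142. That is 0.043 at r = 0.3, 0.071 at r = 0.5, 0.100 at r = 0.7 and 0.114 at r = 0.8, or about 11%, 18%, 25% and 28% of the 0.40 target.

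**Step 4: the larger expected sample.** The abstract estimates 750 dyads. If all entered and 15% were lost, 750 × 0.85 = 637.5 would complete, about 319 per arm. Power for 0.40 would be about 88% without the baseline value and about 95% with it at r = 0.5.

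**The case against.** **Nothing is stated wrongly.** Under randomisation, comparing 36-month means with adjustment for the stratification factor is unbiased, and the sample size agrees with it. This stands. A reader might infer that the primary analysis is biased or the trial underpowered; Step 1 shows that neither follows. The point is about efficiency.

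**The article does not say that nothing else enters the model.** It is a condensed account, and the mention of multivariable models could leave room for more covariates. But it does specify the primary adjustment, and the wording that secondary analyses add exact age implies a short primary set. Omission of baseline BMI is the likelier reading, though it is an inference. The secondary mixed model may bring in the 24-month value, but it is tied to loss to follow-up and would not change the primary estimate.

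**The gain rests on an assumed r.** This stands. A reader might conclude that much of the available precision is lost. That needs r of about 0.5 or more; at r = 0.3 the variance falls by only 9%. The gain in power is also smaller if the trial reaches the expected 750, as Step 4 shows.

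**Stronger readings that the article does not support.**
- An imbalance does not pass in full into the estimate. It carries through multiplied by about r, and the planned standard error already allows for such chance variation.
- Study 1 carry-over is not a reason for this change. Stratified randomisation balances it and the Study 1 term adjusts for it.
- The argument does not extend to every secondary outcome. The article does not list the items of the 24-month survey, so matching baseline values are an inference. For binary outcomes analysed by logistic regression, a prognostic covariate changes the conditional odds ratio being estimated, so the precision argument does not carry over directly.

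**Conclusion.** The point holds as a recommendation to improve efficiency. The primary analysis as specified is valid and meets its own 80% power, but it leaves unused a baseline measurement that the design makes a condition of entry. At 253 per arm, adding it would raise power for 0.40 kg/m² to about 84%, 90% or 97.6% for r of 0.3, 0.5 or 0.7, and would reduce the influence of chance imbalance. These figures assume SD 1.60 at both ages, a linear relation between the two measurements, and the stated r; only the 36-month SD comes from the article. For BMI z-score the proportional gain is again r², with that measure's own correlation. The conclusion does not depend on r being high: one covariate costs one degree of freedom among about 506 completers, so a low r gives a small gain and no material loss.

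**What to change.** Before any 36-month data are seen, state the primary model as linear regression of 36-month BMI on Study 2 arm, Study 1 group and 24-month BMI. If BMI z-score is the chosen outcome, use the 24-month z-score as the covariate. Leave the sample size unchanged; it becomes conservative. Apply the same form to continuous secondary outcomes for which the 24-month survey recorded the same item. Binary outcomes should not be swept in by the same sentence; any baseline covariate there needs its own decision on which odds ratio is to be reported.

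The cost is a sentence or two in the protocol or analysis plan. No new data or visits are needed, because the 24-month measurement already precedes randomisation.
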